### Eligibility criteria

Consenting participants will be enrolled if they satisfy all inclusion criteria and none of the exclusion criteria. The eligibility criteria are listed in Table 3.

**Table 3 tbl3:** Eligibility criteria.

**Inclusion criteria**
• Pregnant women aged 20–39 years with threatened miscarriage (vaginal bleeding and/or abdominal pain) in the first trimester • Gestational age between 5 and 12 weeks • Euthyroidism or controlled hypothyroidism (based on medical history) • Presence of a viable pregnancy • Presence of intrauterine gestational sac on USG if a urine pregnancy test is first positive within the past two weeks • BMI ≥18 and ≤30 kg/m^2^ • Willingness to provide written informed consent
**Exclusion criteria**
• Pregnant women with inevitable abortion • History of recurrent miscarriage defined as at least two consecutive spontaneous miscarriages • Heavy vaginal bleeding or severe abdominal pain requiring surgical intervention • Presence of intrauterine fetus with a crown-rump length inappropriate for gestational age, with no visible heartbeat, or a mean gestational sac of ≥25 mm with no visible fetal pole on USG • Evidence of ectopic pregnancy • Conceived on gonadotrophins or with the use of assisted reproductive technologies • Abnormalities in the structure of the uterus or amputation of the cervix, or any other genital tract anomalies • Uterine myoma with submucosal location of the node (a clinically significant size as judged by the investigator) • Anembrion or fetal malformations as established causes of loss of previous pregnancies • Other clinically significant causes of miscarriage identified during examination (including but not limited to prepregnancy diabetes, prepregnancy uncompensated thyroid dysfunction, history of malignant tumors or current tumors or psychiatric illnesses) • Known STDs • Administration of enzyme-inducing medicinal products (anticonvulsants, antipsychotics, antidepressants and tranquilizers) or use of psychoactive substances before and during pregnancy • Multiple pregnancy • Known as having an endocervical polyp • Known as having infection such as pneumonia, pyelonephritis or septicemia • Known as having autoimmune diseases such as systemic lupus erythematosus, systemic sclerosis or rheumatoid arthritis • Known as having a coagulation defect • Known as having severe heart, liver, lung, kidney or any other organ disorder • Current or ongoing substance abuse, including alcohol and tobacco, as determined by the investigator • History of chemotherapy or radiotherapy • Known allergy or hypersensitivity to dydrogesterone or oral micronized progesterone • Use of hCG or dydrogesterone or progesterone within one month before study enrollment • Participation in any other clinical trial within 30 days before the study enrollment • Planned participation in any other trial during the entire duration of the study • Refusal or inability to comply with the requirements of the protocol for any reason, including scheduled clinic/hospital visits and laboratory tests • Any other condition(s) which would make the patient, in the opinion of the investigator, unsuitable for the study • Any other clinical condition(s) that, as judged by the investigator, contradict(s) inclusion criteria, may lead to early termination of the subject’s participation in the study or make it difficult to interpret the results obtained in the study

BMI, body mass index; hCG, human chorionic gonadotrophin; USG, ultrasonography; STDs, sexually transmitted diseases.

### Sample size

A total of 302 subjects are required to detect a difference of 5% (Siew *et al.* 2018) in miscarriage rate between the two treatment arms, with a confidence level of 95%, power of 80% and noninferiority margin of 15%, taking into account an anticipated dropout rate of 8%. The enrolled subjects will be assigned equally to the four strata (as described below) within each treatment arm; therefore, the sample size has been selected as 304. Thus, 152 subjects would be required in each treatment arm at baseline.

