## Objectives

The primary objective of the study is to compare reduction in miscarriage rate before 20 weeks of gestation between the two treatment arms. The secondary objectives are to compare the following between the two treatment arms: rate of ongoing pregnancy at 24 weeks, rate of live births, safety of the study medications based on TEAEs, levels of immunomodulation markers and time to symptom resolution (Table 1).

**Table 1 tbl1:** Study objectives.

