### Randomization

All enrolled subjects will be randomized in a 1:1 allocation ratio to receive either oral dydrogesterone or oral micronized progesterone. A computer-generated central randomization list will be divided among the study sites. Randomization will ensure that there is equal participation of subjects aged ≤30 and >30 years, and equal participation of subjects with body mass index (BMI) ≤25 and >25 kg/m^2^ within each treatment arm. To attain this, stratified randomization technique will be used. There will be four strata within each treatment arm: (a) age ≤30 years, BMI ≤25 kg/m^2^; (b) age ≤30 years, BMI >25 kg/m^2^; (c) age >30 years, BMI ≤25 kg/m^2^; and (d) age >30 years, BMI >25 kg/m^2^.

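### The sample-size sentence joins detection of a 5% difference to a 15% non-inferiority margin; 302 women give far less than 80% power to detect 5 points and fit only a non-inferiority calculation whose inputs are not stated

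*Protocol article*

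**What the plan says.** The Sample size section states: "A total of 302 subjects are required to detect a difference of 5" percent in miscarriage rate between the arms, citing a pilot study for that figure. The sentence goes on "with a confidence level of 95%, power of 80% and noninferiority margin of 15" percent, and allows for 8% dropout. The total is then raised to 304 so that it divides over the four strata: "Thus, 152 subjects would be required in each treatment arm at baseline".

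The section gives no expected miscarriage rate in either arm, no sign for the 5%, and no statement of whether the 95% confidence level is one- or two-sided.

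Non-inferiority is mentioned nowhere else in the article. The Objectives section says "The primary objective of the study is to compare reduction in miscarriage rate before 20 weeks of gestation between the two treatment arms", and Table 1 repeats this. Statistical methods names McNemar's test or the Chi-square test for categorical variables. The Treatment section makes dydrogesterone the test arm and micronized progesterone the reference.

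**The concern.** Detecting a 5-point difference means rejecting equality when the true rates differ by 5 points. A 15-point margin means ruling out that the test arm is worse by 15 points or more. The two hypotheses need different sample sizes, and a margin plays no part in the first.

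Because the objective and the named tests are those of a plain comparison, a reader has every reason to take the sentence at its word, as 80% power to detect 5 points. A non-significant Chi-square result on the primary endpoint could then be read as ruling out a difference of that size. Equally, non-inferiority could be claimed or dropped once the data of this open-label trial are known, since only the sample-size sentence commits to it.

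**Working it through.** **Inputs from the article.** Total 302, difference 5 points, 95% confidence, power 80%, margin 15 points (taken as absolute), dropout 8%, allocation 1:1. Evaluable women: 302 × 0.92 = 277.8, or about 139 per arm.

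**Assumed input.** No planning rate is given. I use 11%, the Introduction's background figure for loss after a live fetus has been seen, and vary it from 5% to 30%.

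**1. Can 302 be reproduced?** Not from the stated inputs alone, because the event rate is missing. Steps 2 and 3 ask which rates would produce it.

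**2. Literal reading: detect 5 points, two-sided 5%.**

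n per arm = [1.960·√(2p̄q̄) + 0.842·√(p₁q₁ + p₂q₂)]² / (p₁ − p₂)²

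Power = Φ{[|p₁ − p₂|·√139 − 1.960·√(2p̄q̄)] / √(p₁q₁ + p₂q₂)}

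For 11% vs 6%: √(2p̄q̄) = 0.3944 and √(p₁q₁ + p₂q₂) = 0.3928.
- n = (0.773 + 0.331)² / 0.0025 ≈ 487.2, so 488 per arm; 976 / 0.92 gives 1,061 in total.
- Power = Φ[(0.5895 − 0.773) / 0.3928] = Φ(−0.467) = 32%.

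| Rates | Power at 139 per arm | Per arm for 80% | Total with 8% dropout |
|---|---|---|---|
| 5% vs 10% | 35% | 435 | 946 |
| 6% vs 11% | 32% | 488 | 1,061 |
| 11% vs 16% | 23% | 733 | 1,594 |
| 30% vs 35% | 14% | 1,377 | 2,994 |

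A one-sided 5% test reaches at most 48% over the same range. Power comes near 80% only if one arm has almost no miscarriages (0% vs 5%: 76% two-sided, 85% one-sided).

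**3. Non-inferiority reading.** With d = the true excess in the dydrogesterone arm:

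n per arm = (z₁₋α + 0.842)² · (p_C q_C + p_T q_T) / (0.15 − d)²

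The squared term is 7.849 at one-sided 0.025 and 6.183 at one-sided 0.05. Solving for the variance sum that gives 139 per arm:
- **d = +5 points (dydrogesterone worse).** One-sided 0.025: 139 × 0.01 / 7.849 = 0.177, a control rate of about 7.5%. One-sided 0.05: 139 × 0.01 / 6.183 = 0.225, about 10.5% (vs 15.5%).
- **d = 0.** One-sided 0.025: 139 × 0.0225 / 7.849 = 0.398, about 27.5% in both arms. One-sided 0.05: approached only at rates of about 42% to 50%.
- **d = −5 points (dydrogesterone better).** One-sided 0.025: 139 × 0.04 / 7.849 = 0.708, above the maximum possible value of 0.5. The largest size any rates can give is 98 per arm.

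**4. Non-inferiority power at 139 per arm if the control rate were 11%.**
- Dydrogesterone at 16%: standard error √(0.2323 / 139) = 0.0409 and 0.10 / 0.0409 = 2.446. Power is Φ(2.446 − 1.960) = 69% with a two-sided 95% interval, and Φ(2.446 − 1.645) = 79% with a one-sided 95% bound. Reaching 80% takes 183 per arm (398 in total) or 144 per arm (314 in total).
- Both arms at 11%: 98% with a two-sided 95% interval.

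**The case against.** The strongest reply is that the authors never ran a superiority calculation. The same sentence states a margin and takes the 5% from a previous study, so the 5% is most naturally the assumed true difference in a non-inferiority calculation. On that reading 302 is coherent: it follows from about 10.5% vs 15.5% at one-sided 0.05. The missing rate and sidedness may stand in a full protocol or analysis plan that the article only condenses.

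Much of this stands. The total can be a correct non-inferiority size, and the omitted inputs would not by themselves be a finding. What it does not repair is the sentence itself, which attaches 80% power to detecting 5 points, and that is untrue at any plausible rate. Nor do the objective and the named tests point a reader to the non-inferiority reading.

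Three stronger inferences are tempting, and the article supports none of them.
- **That 302 is too few for non-inferiority.** Step 3 shows sets of rates at which it gives 80%.
- **That non-inferiority misses 80% at the trial's own event rate.** The 11% is background in the Introduction and is not offered as a planning rate. The 69% depends on that rate, on dydrogesterone being 5 points worse, and on a two-sided 95% interval.
- **That the number works only if dydrogesterone is 5 points worse.** Equal arms near 27.5% also give it, and assuming the test arm slightly worse is a cautious choice, not a fault.

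**Conclusion.** The sentence is wrong as written. It joins two incompatible aims, and its literal power claim fails by a wide margin: 14% to 35% in place of 80% for lower-arm rates of 5% to 30%. That conclusion does not depend on the assumed 11%; only the required totals of about 1,060 to 1,590 women do.

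The size of 304 is not shown to be inadequate for non-inferiority. Whether it is generous, on target or short turns on the planning rates, the sign of the 5% and the alpha. With an 11% control rate, these choices move power from 69% to 98% under a two-sided 95% interval alone. All non-inferiority figures assume an absolute 15-point margin and the unpooled normal approximation.

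**What to change.** Keep 304 women and make these changes:
- **Sample size.** Remove the wording about detecting a 5% difference. State that the size is for non-inferiority of dydrogesterone to micronized progesterone at an absolute margin of 15 points. Give the authors' own planning rate in each arm, the sign of the 5%, the one-sided alpha, and the power that these inputs give. The 11% and 69% above are illustrations and should not be written in as the planning values.
- **Objectives and Table 1.** Word the primary objective as non-inferiority.
- **Statistical methods.** Make the primary analysis a confidence interval for the risk difference, at the level matching that alpha, compared with the margin, in place of a Chi-square test of equality.
- **Limitation.** State that the trial is not powered to detect a 5-point difference.

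The cost is rewording in the protocol and, where it carries the same text, the registry entry, together with a less favourable power statement. No extra patients are needed. A much larger trial would be needed only if detecting 5 points is truly the aim.

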### Randomization

All enrolled subjects will be randomized in a 1:1 allocation ratio to receive either oral dydrogesterone or oral micronized progesterone. A computer-generated central randomization list will be divided among the study sites. Randomization will ensure that there is equal participation of subjects aged ≤30 and >30 years, and equal participation of subjects with body mass index (BMI) ≤25 and >25 kg/m^2^ within each treatment arm. To attain this, stratified randomization technique will be used. There will be four strata within each treatment arm: (a) age ≤30 years, BMI ≤25 kg/m^2^; (b) age ≤30 years, BMI >25 kg/m^2^; (c) age >30 years, BMI ≤25 kg/m^2^; and (d) age >30 years, BMI >25 kg/m^2^.

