### Statistical methods

All data analysis will be carried out as per comprehensive statistical analysis plan and based on the ICH E9 document ‘Statistical Principles for Clinical Trials’. All statistical analyses will be done using the Statistical Package for Social Sciences (SPSS; IBM Corp., USA). Continuous variables will be checked for normality and analyzed using paired t-test if the distribution is normal, or Wilcoxon signed rank test otherwise. Descriptive statistics and proportions will be used to summarize the population in each treatment arm/subgroup. Categorical variables will be analyzed using McNemar’s test or Chi-square test, as applicable. Regression analysis will be used to analyze the association between variables. Incidence of AEs will be reported as the proportion of subjects reporting them.

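### Stratified randomisation cannot make the four age/BMI strata equal in size, as the protocol says it will; no enrolment cap is stated, and a cap would conflict with the eligibility rule

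*Protocol article*

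**What the plan says.** The Randomization section gives a 1:1 allocation and then states: "Randomization will ensure that there is equal participation of subjects aged ≤30 and >30 years". It makes the same promise for BMI up to and above 25 kg/m², and names the means: "within each treatment arm. To attain this, stratified randomization technique will be used". The strata are the four combinations of age (up to or above 30 years) and BMI (up to or above 25 kg/m²).

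The Sample size section repeats the idea: "The enrolled subjects will be assigned equally to the four strata (as described below) within each treatment arm". It gives this as the reason for moving from 302 to 304 women, 152 per arm.

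The Eligibility criteria section enrols consenting women who meet all inclusion criteria and no exclusion criterion. Table 3 has no limit on any age or BMI stratum.

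On analysis, the Statistical methods section says "Categorical variables will be analyzed using McNemar’s test or Chi-square test, as applicable". It also mentions regression without naming covariates, and it refers to a comprehensive statistical analysis plan that is not shown.

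**The concern.** Age and BMI are traits a woman brings to the trial, so nobody can be assigned to a stratum. Randomising within strata settles which arm each woman joins. The number of women in each stratum depends on who presents and is enrolled. The protocol therefore credits the randomisation with a property it does not have.

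Sites are already screening and enrolling. A reader who takes the text at face value must either expect equal strata that will not appear, or begin closing strata when they fill. The second course would refuse women whom the eligibility rule admits, and recruitment would run at the pace of the rarest stratum. The stated reason for the final sample size also rests on the mistaken property.

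**Working it through.** **1. The plan's own figure.** Inputs from Sample size and Randomization: 302 women, 4 strata, 2 arms, hence 4 × 2 = 8 cells.
- 302 / 8 = 37.75, rounded up to 38 per cell.
- 38 × 8 = 304; 304 / 2 = 152 per arm; 304 / 4 = 76 per stratum.

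This reproduces 304 and 152, so equal stratum sizes are meant literally. (302 itself cannot be checked, because the article gives no planning miscarriage rate and no sidedness.)

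**2. Equal strata without a cap.** Take the most favourable case, in which each stratum holds exactly 25% of eligible women. The multinomial probability of 76 in each is 304! / (76!)⁴ × 0.25³⁰⁴ ≈ 0.0002.

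Exact equality is a strict standard, so consider the expected split too. Assume 30% aged over 30 and 40% with BMI above 25, independently. The stratum shares are 0.7 × 0.6 = 0.42, 0.7 × 0.4 = 0.28, 0.3 × 0.6 = 0.18 and 0.3 × 0.4 = 0.12. Of 304 women, that is about 128 / 85 / 55 / 36 rather than 76 each.

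**3. Equal strata with a cap of 76.** The rarest stratum, with share f, needs about 76 / f eligible women to fill. The expected number until all four strata are full was simulated as the largest of four negative binomial filling times (4,000 runs, age and BMI independent). Women refused = that number − 304.

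| Assumed share aged >30 / BMI >25 | Smallest f | 76 / f | Simulated number needed | Refused |
|---|---|---|---|---|
| 50% / 50% | 0.25 | 304 | 335 | 31 |
| 40% / 40% | 0.16 | 475 | 475 | 171 |
| 30% / 40% | 0.12 | 633 | 635 | 331 |

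As a share of eligible women, refusals run from 31 / 335 ≈ 9% to 331 / 635 ≈ 52%. The simulation treats the four filling times as independent. Repeating it with women drawn one at a time gives about 341 needed (341 − 304 = 37 refused) in the first row and makes no material difference in the other two.

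**4. Analysis that does not use the strata.** Assume stratum miscarriage risks of 6%, 9%, 15% and 22%, equal in both arms, with 38 women per cell (50,000 runs, nominal two-sided 0.05). Type I error is 0.0455 for the plain chi-square and 0.0496 for the Cochran-Mantel-Haenszel test. Monte Carlo standard error is √(0.05 × 0.95 / 50,000) ≈ 0.001. The plain test is slightly conservative and remains valid.

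**The case against.** The best defence is that the authors meant only balance between arms, since the text says the equality holds in each treatment arm. The rounding to a multiple of eight rules this out: it is needed only if all eight cells are to be the same size.

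A second defence is that balanced enrolment by age and BMI can be deliberate, for instance to support the subgroup summaries that Statistical methods mentions. That is legitimate, but it is a recruitment decision that needs a stated cap.

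A reader might go further than the documents allow in three ways.
- **That quotas are turning women away.** No quota or stratum-closing rule is written, and the article gives no age or BMI distribution. Which stratum is rarest, and every refusal figure above, is conditional on assumed shares and on an unwritten cap.
- **That the analysis ignores the strata.** The chi-square line covers categorical variables in general and does not name the primary test. Regression is mentioned and a separate analysis plan is cited. Silence in a condensed article does not show that the strata are dropped.
- **That leaving out gestational age at entry is a defect.** Entry at 5 to 12 weeks leaves 20 − 5 = 15 down to 20 − 12 = 8 weeks at risk, so it is a sensible covariate. Not stratifying on it is a design choice that contradicts nothing in the text. In a simulation with assumed inputs (278 women, 10% events, odds falling 26% per week), adjustment lowered the variance by only about 4%.

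**Conclusion.** The point holds as an error of statement in the Sample size and Randomization sections, and as a conflict between the promised equality and an eligibility rule with no caps. That much rests on the documents alone.

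Its size is modest. The effect on the sample size is 304 − 302 = 2 women. Neither the treatment comparison nor the type I error is put at risk. The practical cost arises only if sites act on the wording by closing strata. It could then range from a few dozen refused women to more than half of those eligible, depending on an age and BMI mix that the article does not give. The analysis plan would not settle this, because it concerns enrolment and randomisation.

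**What to change.** 1. In Randomization and Sample size, replace the equal-participation and equal-assignment wording with a statement that randomisation is stratified by age and BMI to balance the arms within each stratum. Let the strata fill naturally.
2. Restate the basis for 304: 302 are needed and the number was rounded up. Without equal strata, 302 (151 per arm) already suffices on the plan's own inputs, so the extra two women do no harm.
3. If a cap is really intended, state it openly with its recruitment consequences, and reconcile it with the Eligibility criteria section.
4. As a free improvement, estimate the primary risk difference stratified by the four randomisation strata (for example Mantel-Haenszel) rather than by a plain chi-square. Adjustment for gestational age at entry is optional.

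The cost is a few sentences and a few lines of analysis code. With natural filling, descriptive subgroups will have less equal precision.

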### Treatment

Subjects in the test arm will be treated with oral dydrogesterone; the first dose will be 40 mg (stat) and subsequent doses will be 10 mg three times a day. Subjects in the reference arm will be treated with oral micronized progesterone at a dosage of 200 mg two times a day. Except for subjects who face miscarriage within 14 weeks of gestation, rest will be treated up to one week after stoppage of bleeding or if bleeding does not stop, then treatment will be continued till a maximum of 14 weeks of gestation. Continuation of treatment beyond this will solely be at the discretion of the treating physician. If relapse of bleeding is observed after stoppage of treatment, the physician may decide to continue the medication at his/her discretion; relevant details will be recorded.

### Schedule of visits

A total of seven visits are planned in this study: three in the first trimester, three in the second trimester and one after delivery. The schedule of visits is represented graphically in Fig. 1. Treatment will be initiated at Visit 1 and completed at Visit 4 (except for subjects with prolonged treatment based on physician’s discretion); a window period of +3 days is permissible for Visit 4. Visit 7 will be conducted after delivery. In addition to these scheduled visits, subjects may consult the investigator for any emergent situation during study participation.

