**Abstract:**

Threatened miscarriage is a common complication of early pregnancy characterized by symptoms of vaginal bleeding with/without abdominal cramps/pain in the first trimester. Progestogens are often administered for the management of this condition. Presented herein is the protocol of an ongoing, multicentric clinical trial to investigate the efficacy and safety of micronized progesterone (natural progestogen) compared to dydrogesterone (synthetic isomer of progesterone). A total of 304 eligible pregnant women aged 20–39 years, diagnosed with threatened miscarriage, will be enrolled during 5–12 weeks of gestation and randomized equally to receive either oral dydrogesterone (40 mg stat, followed by 10 mg three times a day) or oral micronized progesterone (200 mg two times a day) up to one week after stoppage of bleeding or if bleeding does not stop, then treatment will be continued till a maximum of 14 weeks of gestation (unless miscarriage is confirmed earlier or the investigator decides to prolong treatment for better outcome or if bleeding relapses). Scheduled visits after enrollment will be conducted during 6–13, 8–14, 18–20 and 24–26 weeks of gestation, in addition to a visit at the end of treatment at 14 weeks and another after parturition. The primary endpoint of the study is the miscarriage rate before 20 weeks of gestation. Secondary endpoints include the ongoing pregnancy rate at 24 weeks, treatment-induced changes in serum levels of cytokines and time to symptom resolution. Apart from the incidence of treatment-emergent adverse events, safety endpoints include changes in complete blood count and the results of liver and kidney function tests from baseline to 14 and 24–26 weeks of gestation. Delivery outcomes are exploratory endpoints of the study.

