The current study aims to combine the knowledge gained from the above studies and overcome some of their limitations. Accordingly, a multicentric, prospective clinical trial has been designed to compare oral dydrogesterone versus oral micronized progesterone in threatened miscarriage, wherein patients will be treated not for any predefined duration but till one week after stoppage of bleeding or if bleeding does not stop, then treatment will be continued till a maximum of 14 weeks of gestation (unless miscarriage is confirmed within 14 weeks of gestation or the investigator decides to prolong treatment for better outcome or if bleeding relapses). In addition to investigating miscarriage rates, symptom resolution, delivery outcomes and treatment-emergent AEs (TEAEs), this study aims to compare the immunomodulatory roles of the molecules being investigated by the assessment of cytokine levels as this aspect has not been explored in any of the aforementioned studies (Siew *et al.* 2018, Lou *et al.* 2021, Verma & Yadav 2021, Shaikh *et al.* 2022).

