**Secondary endpoints**
• Ongoing pregnancy rate at 24 weeks • Change in serum levels of cytokines (IL-4, IL-10, IFN-γ and TNF-α) from baseline to the end of treatment • Time to symptom (vaginal bleeding and/or abdominal pain) resolution

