**Figure 1 fig1:**
[figure not shown]
Schedule of visits. All study subjects will be screened and enrolled at Visit 1 (at 5–12 weeks of gestation) after obtaining written informed consent. Visit 2 will be conducted between 6 and 13 weeks and Visit 3 between 8 and 14 weeks of gestation. Visit 4 will be conducted at the end of 14 weeks of gestation, with a permissible window period of +3 days. Visits 5 and 6 will be conducted at 18–20 and 24–26 weeks of gestation, respectively. Visit 7 will be conducted after parturition.

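### The cytokine endpoint runs to the end of treatment, but the protocol puts that end both one week after bleeding stops and at the 14-week visit

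*Protocol article*

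**What the plan says.** Three places let each woman's bleeding decide when treatment ends.

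- **Treatment section:** apart from women who miscarry within 14 weeks, the "rest will be treated up to one week after stoppage of bleeding or if bleeding does not stop", in the latter case to 14 weeks at most. Going on beyond that, or after a relapse, is left to the physician.
- **Introduction:** this is presented as a deliberate feature of the design: "patients will be treated not for any predefined duration but till one week after stoppage of bleeding".
- **Abstract:** the same rule is given in full.

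Two places fix the end at 14 weeks.

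- **Schedule of visits:** "Treatment will be initiated at Visit 1 and completed at Visit 4", with one exception: "except for subjects with prolonged treatment based on physician’s discretion". The legend of Figure 1 dates that visit: "Visit 4 will be conducted at the end of 14 weeks of gestation, with a permissible window period of +3 days".
- **Abstract:** besides the bleeding-based rule, it lists "a visit at the end of treatment at 14 weeks".

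Table 2 defines the cytokine endpoint (IL-4, IL-10, IFN-γ, TNF-α) as change "from baseline to the end of treatment" and names no week or visit. In the same table, the liver and kidney function tests have stated gestational weeks: 14 and 24–26. The Abstract and Discussion call the cytokine changes treatment-induced.

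**The concern.** Under the bleeding-based rule, a woman whose bleeding stops early finishes treatment before Visit 4. The exception in the Schedule of visits section covers treatment that lasts longer, not treatment that ends sooner, so it does not remove the conflict. The end of treatment in Table 2 can then mean Visit 4 or each woman's own last dose. These are different measurements.

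The Introduction presents cytokines as the aspect that the earlier comparisons of these two drugs left unexplored. A sample taken some weeks after the last dose in some women and on drug in others does not measure one quantity that can be called treatment-induced. Time to symptom resolution is itself a secondary endpoint compared between arms, so the length of treatment, and with it the time off drug, is partly an outcome of treatment.

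**Working it through.** The plan gives no figure to reproduce here. The check is arithmetic on its own schedule.

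**Inputs from the protocol.** Entry at 5–12 weeks of gestation (Figure 1 legend); treatment for one further week after bleeding stops, with a ceiling of 14 weeks (Treatment section); Visit 4 taken as week 14.0 (Figure 1 legend).

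**Assumption, not in the protocol.** Weeks from entry to stoppage of bleeding, *b*, varied from 0.5 to 4. Relapse and discretionary prolongation are left out; either would shorten or remove the gap for the women concerned.

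**Formulas.**
- Stop week = min(entry week + *b* + 1, 14)
- Weeks off drug at Visit 4 = 14 − stop week

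**Reading 1: sample at Visit 4.** Example: entry at week 6 with *b* = 1 gives a stop at 6 + 1 + 1 = 8 and a gap of 14 − 8 = 6 weeks.

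| Entry week | b = 0.5 | b = 1 | b = 2 | b = 3 | b = 4 |
|---|---|---|---|---|---|
| 5 | 7.5 | 7 | 6 | 5 | 4 |
| 6 | 6.5 | 6 | 5 | 4 | 3 |
| 8 | 4.5 | 4 | 3 | 2 | 1 |
| 10 | 2.5 | 2 | 1 | 0 | 0 |
| 12 | 0.5 | 0 | 0 | 0 | 0 |

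With *b* = 1, the gap runs from 0 weeks (entry at week 12) to 7 weeks (entry at week 5). If the end of 14 weeks means 14 weeks and 6 days, and the 3-day window is used in full, the gap grows by up to 9/7 ≈ 1.3 weeks. Where the ceiling does not bind, each extra week of bleeding shortens the gap by one week.

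**Reading 2: sample at the last dose.** The off-drug gap disappears, but gestational age at sampling equals the stop week. With *b* = 1, that is week 7 for entry at week 5 and week 14 for entry at week 12. Exposure is the stop week minus the entry week: for entry at week 5 it runs from 1.5 weeks (*b* = 0.5) to 5 weeks (*b* = 4). Both quantities depend on how fast bleeding stops and could differ by arm. The visits described in the text are set by gestational age; none is tied to a woman's last dose.

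**The case against.** The strongest reply is that the stopping rule is consistent wherever it is stated in full, that the Abstract gives it before mentioning the 14-week visit, and that the Schedule of visits sentence only names loosely the outer limit of treatment. As an account of how the sentence arose, that is plausible. It does not rescue the endpoint, because Table 2 relies on the same term and gives no week.

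Figure 2, which lists the activities at each visit, is not shown and may fix the cytokine draw. This stands as a limit: the sampling visit cannot be confirmed. Still, a draw placed at Visit 4 would not become the end of treatment for women who had already stopped.

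Three stronger readings are tempting, and the documents do not support them.

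- **That the comparison between arms is biased, with women on dydrogesterone longer off drug.** The Introduction reports better symptom relief or resolution on dydrogesterone, not earlier resolution, and from studies with preset treatment periods. A comparison at a fixed gestational week is also a valid randomised comparison of two treatment policies. Stopping early because bleeding stopped is part of the policy.
- **That many women will be long off drug, or that the effect is diluted by some amount.** The protocol gives neither the distribution of entry weeks, nor the duration of bleeding, nor how long cytokine changes last after the last dose. At entry in week 10 the gap is only 0–2.5 weeks, and in week 12 only 0–0.5.
- **That the draw should move to an earlier visit.** Visits 2 and 3 are gestational windows (6–13 and 8–14 weeks), so neither guarantees that every woman is still on drug. Enrolment is under way, so a move would split the sample between two sampling times.

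**Conclusion.** The point holds as a conflict in the running text that leaves a named secondary endpoint without a consistent time point. At Visit 4, women could be anywhere from on drug to about 7 weeks off it (assuming bleeding stops one week after entry, for entry at weeks 12 down to 5), or 0 to 7.5 weeks if time to stoppage is varied from 0.5 to 4 weeks. A Visit 4 result therefore cannot be called an end-of-treatment or treatment-induced change for all women. A last-dose result would mix gestational ages and exposures. A difference between arms in off-drug time is possible but not established. The primary endpoint, miscarriage before 20 weeks, does not depend on this. The change should be made, but it is one of definition and interpretation.

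**What to change.** 1. Reconcile the Abstract, the Treatment section and the Schedule of visits section on when treatment ends. This review takes no position on which rule is right.
2. Define the cytokine endpoint at one time point common to both arms. One option is to keep a 14-week sample and name the endpoint change from baseline to 14 weeks of gestation, in the way Table 2 already does for liver and kidney function tests.
3. Interpret it as a treatment-policy comparison, and drop the treatment-induced wording in the Abstract and Discussion.
4. Adjust the comparison between arms for baseline cytokine level and gestational age at entry. Both are fixed before treatment. Time off drug arises after randomisation and should not be used as an adjustment variable.

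**Cost.** Wording in the protocol and the analysis plan. If the sample is already drawn at Visit 4, no visit or blood draw is added or moved. The scientific price is that the endpoint no longer supports a claim about immunomodulation while on drug.
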